**How are sepsis survivors identified in your hospital?**
1. Who is involved in clinical documentation and coding that the patient has/had sepsis?
o What do you do with the information? How is it shared/alerted and with whom?
2. What IT systems/tools are used?
o How are the IT systems used? (what function do they complete?)
o Criteria used to code sepsis categories?
3. How is success in identifying sepsis patients monitored?
4. What is your accuracy rate for identifying sepsis patients?
o How do you measure accuracy?
5. What are the steps in identifying sepsis patients that you think need improvement? Why?
o What is needed to achieve improvement?
6. What strategies were tried and failed?
7. What are the successful strategies?
8. What are the barriers to identification, IT documentation and communication, accuracy, monitoring accuracy?
9. To make improvements in this process, who should we work with?
10. How is sepsis defined in your hospital?
**Objective 2. Determine the workflow for referral of sepsis survivors to home health care**
What is the process for identifying sepsis survivors for referral to home health care?
1. What criteria are used to determine the need for home health referral?
2. Who is involved in making this decision?
3. When is the decision to refer the patient for home care made?
4. What IT tools are used?
5. What are the barriers to getting sepsis survivors to home health care?
6. What are some ways we could improve the process?
7. What resources are needed for improvement?
8. What are the similarities in this process across units/floors? What are the differences?
9. To make improvements in this process, who should we work with?

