Our I-TRANSFER intervention is designed to address several barriers and gaps that may jeopardize the implementation of early post-acute surveillance. Sepsis survivors are not consistently identified with a medical diagnosis of sepsis until after discharge from acute care [51–55]. This results in the diagnosis and other patient characteristics not being adequately communicated to the next level of care [1, 39, 40, 56]. Home health clinicians likely do not know they are receiving a sepsis survivor. Second, there is little evidence to guide the transition of sepsis survivors to HHC. Our protocol is designed to provide a critically needed, especially post-pandemic, best practice intervention model to clinicians and the HHC industry nationwide. This protocol is even more timely given the pandemic, as research suggests that COVID-19 can lead to sepsis [57] and many hospitalized patients prefer to recover at home due to skilled nursing facility capacity and safety concerns [58]. Third, among sepsis survivors transitioned to HHC, and not readmitted within the first week, only 28% received the early visit protocol, shown by our team to be associated with significantly reduced readmissions [24]. This presents an important opportunity to generate further evidence of effectiveness and inform widespread implementation to help many more sepsis survivors. Our advisory group, comprised of national leaders in sepsis care and HHC professional organizations will facilitate widespread dissemination of our findings, from academic nursing and medicine to industry practitioners.

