Implementation of the I-TRANSFER components will be guided by the stakeholders and research team using intervention mapping, as described below. The context and determinants (barriers, enablers), processes, and strategies encountered during Aim 1 will be collected for Aim 2 analysis. Hospital partners will work with the study and HHC team to achieve the following components of I-TRANSFER: identify the sepsis survivors during the hospitalization, make the outpatient follow-up appointment before discharge, notify the HHC agency of a sepsis survivor, conduct timely home health visits and outpatient visits in week one. Based on our preliminary work, we have identified several effective strategies that we can suggest to better identify the sepsis survivor, including generalizable use of sepsis order sets within the electronic health record [14]. We will also recommend use of the Centers for Disease Control (CDC) Epicenters Sepsis Clinical Surveillance Definition, which has the advantage of identifying confirmed cases of sepsis given the criteria of sustained antibiotic delivery [35, 77, 78]. We will examine fidelity to these recommended components as potential implementation enablers.

Challenges we expect to face in making and achieving a timely outpatient visit are limited appointment availability, and patients who cancel or do not attend the visit. A potential strategy is to increase awareness about I-TRANSFER’s evidence and include a script for the clinician to educate the patient about the value and importance of the outpatient visit. Transportation may be an issue as well and will be brainstormed for solutions with the stakeholders and tracked as a barrier. Hospital based personnel will notify the HHC intake department when the patient is a sepsis survivor. The intervention mapping will determine the workflow for this component with each site. It may include phone calls, text messaging, faxed or electronic documents.

HHC intake personnel will likely schedule the nurse visits and notify the visiting nurse of the sepsis diagnosis and date of the outpatient appointment. To meet protocol, the first registered nurse home visit will occur within 2 days of hospital discharge, with a second visit that week. The patient will be encouraged and assisted if necessary (e.g. transportation) to attend their scheduled outpatient appointment.

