### Study sample

#### Aim 1, effectiveness of the I-TRANSFER intervention

Sample sizes needed to provide sufficient power were calculated using Stata [79]. Preliminary unpublished data of a national sample show on average a 23% 30-day readmission rate for sepsis survivors in HHC. Our previous study showed a 7-percentage point or 41% relative reduction among those receiving early visits [24], and other studies report that 22–45% of readmissions are preventable [80]. Therefore, to detect a 7-point reduction (30.4% relative decrease) in the readmission rate under the intervention we would require an average of 400 patients per time interval. Current estimates from the sites give us 869 per period.

The I-TRANSFER intervention is targeted at the hospital and HHC agency and is considered part of clinical care implemented for all sepsis survivors. There is no individual patient recruitment, prospective assignment, or primary data collection from patients. The analysis will be completed on existing datasets. We will analyze a sample drawn from all Medicare fee-for-service sepsis survivors discharged to HHC during a 4-year period (01/01/2021 and 12/31/2024). Analyses from our 2013–14 dataset suggests that without exclusions there will be approximately 800,000 sepsis discharges per year who receive HHC [24].

Ten clinical sites located in the United States have committed to participate as dyads, 5 referring hospitals and their 5 partnered home health agencies. Sites were selected based on our relationships with staff, ownership status (hospital owned or free-standing), commitment to appoint an implementation team, size, geography, and diversity (academic and community). We sought regional diversity with sites in the East and West. To be eligible HHC agencies must be Medicare certified to generate claims and confirm a hospital referral source as a partner.

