### Data sources and collection

#### Aim 1, effectiveness of the I-TRANSFER intervention

A national sample of Medicare administrative, home health OASIS and claims data from CMS Chronic Condition Warehouse (CCW) will be employed (Table 1). This will yield detailed information about the index hospital stay, subsequent HHC and outpatient provider services and outcomes. It also will provide information about the characteristics of hospitals and admitting HHC agencies, and the health care market areas where patients live. The CCW maintains calendar year files so we will request files between 01/01/2021 and 12/31/2024. We will request CCW data on all Medicare beneficiaries with a claim for a HHC service provided one year prior to the start of the study to 6 months after the end. Within these data sets, we will identify the sepsis survivors transitioned from participating hospitals to their partner HHC agency by merging the Provider of Service File with the claim files. The additional sepsis survivors found in the CCW data, not associated with our participating institutions, will serve as additional controls.

**Table 1 Tab1:** Variables Obtained from the Medicare Claims and OASIS Home Health Admission Files

Data	Source
*Physician, Home Health Agency and Hospital Characteristics*	
Physician specialty	Downloadable National Provider Identifier File (CMS)
Home Health Agency and Hospital Ownership	Provider of Services File
Home Health Agency and Hospital Control/auspices (for- profit/non-profit/public)	Provider of Services File
Size of home health agency, # of annual admissions	Provider of Services File
*Beneficiary Sociodemographic, Clinical and Cost Variables*	
Demographics	Medicare Beneficiary Summary File; OASIS
Informal support	OASIS
Living arrangements	OASIS
Eligible for Medicare and Medicaid	Medicare Beneficiary Summary File
Health care use and cost (ie. Medicare program payments)	MedPAR/Medicare Parts A and B SAF claims
Medical diagnoses ICD codes, acute and HHC	MedPAR/Medicare Parts A and B SAF claims; OASIS
Index hospital length of stay	MedPAR
Cognitive, physical, sensory function	OASIS
*Early Nursing and Outpatient Provider Visits Following Index Hospital Discharge*	
Timing and number of home health visits	Medicare Home Health SAF claims
Timing of first physician, physician assistant or nurse practitioner visit for outpatient evaluation & mgt	Mediare Part B SAF claims

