Implementation Mapping. The systematic process of implementation mapping has 5 steps for developing strategies to improve adoption, implementation, and maintenance of evidence-based interventions in the real world [64]. These steps will be informed by the needs assessments, the CFIR interviews with stakeholders and the ORIC survey. Step 1 calls for an implementation needs assessment of eight objectives to identify barriers and enablers, adopters, and implementers (Table 2). At the end of this step, we will know who the champions will be, who will make resources available, and who are the decision makers. In Step 2, together with the dyads, we generate adoption and implementation outcomes and performance objectives, identify determinants, and create matrices of change objectives. This step determines who must do what and how will success be measured. For example, the hospital case managers may be tasked with determining the workflow and strategies for making the follow-up outpatient appointment and educating sepsis survivors on its importance. Matrices of change objectives answer what must change to make something happen [64]. Each performance objective related to I-TRANSFER (e.g., identify the survivors, communicate with HHC, make the appointment, etc.) and its determinants, identified in earlier steps, will be placed on a grid with corresponding person(s) responsible. Third, we will select implementation strategies for each component of I-TRANSFER. In addition to using our teams’ wisdom, we will turn to the literature using resources such as the taxonomy of theory-based methods applicable to individual and organizational levels [70, 79, 81–83]. While the exact strategies to be employed will depend on the findings of this period of data collection, it is likely that they will consist of a multifaceted approach to implementation including staff education via webinar or in-person, changes to organizational processes and workflow, information technology, and the provision of audit and feedback to clinicians and staff taking part in the implementation study. Fourth we will produce implementation protocols, and in the fifth step we will monitor progress and fidelity during the 12-month implementation phase. While maintaining the core I-TRANSFER elements, in keeping with a pragmatic design, we will allow variation in the workflow for dyad preferences while providing monitoring and feedback of the implementation through the rollout [84]. Implementation mapping is an iterative process where steps will be revisited and modified as needed [64].

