**Objective 3. Map the process for how and when home health is notified about the referral**
How are home health personnel notified that there is a referral to home health?
1. Who gets the notification?
2. When are they notified?
3. How are they notified?
a. Do they know the expected discharge date?
4. What IT tools are used to make the referral?
5. What are the barriers to making the referral to home health care?
6. How are the patient and family involved?
a. Who involves them?
7. We are interested in learning about areas for improvement in the process. What are some areas for improvement for the process of notifying home health of the referral?
a. What resources are needed to make improvements?
8. To make improvements in this process who should we work with?

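### Referral to home health care at the dyads could change during the study, yet the Aim 1 cohort and the claims request as worded hold only survivors who reached home health care, so an unmeasured shift in patient mix would not be removed and the share referred could not be reported.

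*Protocol article*

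**What the plan says.** Table 2 of the protocol article sets out the needs assessment done with each site. Objective 2 concerns the referral workflow. It asks which criteria and which people decide on referral, "What are the barriers to getting sepsis survivors to home health care", and "What are some ways we could improve the process", and then which resources and contacts improvement would need. Objective 3 asks "What are the barriers to making the referral to home health care".

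The paragraph on implementation mapping says of its five steps: "These steps will be informed by the needs assessments, the CFIR interviews with stakeholders and the ORIC survey". The components themselves are in Study design: "identify the sepsis survivors during the hospitalization, make the outpatient follow-up appointment before discharge, notify the HHC agency of a sepsis survivor", followed by timely home and outpatient visits in the first week. A higher referral rate is not among them.

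Two statements fix the Aim 1 population. Study sample: "We will analyze a sample drawn from all Medicare fee-for-service sepsis survivors discharged to HHC during a 4-year period". Data sources and collection: "We will request CCW data on all Medicare beneficiaries with a claim for a HHC service". Dyad patients are those who moved from a participating hospital to its partner agency.

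The Analysis section for Aim 1 reads differently. It starts by finding every sepsis survivor in national hospital data, and only then picks out those who moved to a partner agency.

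**The concern.** Entry to the cohort depends on a decision made at hospital discharge, after the hospital has been exposed to onboarding and intervention. If that decision changes at the dyads, the survivors analysed before and after differ in kind, and an intention-to-treat label does not repair this.

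The planned safeguards address other problems. Time adjustment and concurrent national controls remove trends shared with other providers, not a change at five hospitals. Covariates and entropy balancing deal with measured differences only. The covariate balance check uses baseline observations, so it cannot show a shift that begins at onboarding. The conceptual framework treats the amount of home health and physician service as endogenous, but not entry into home health care. The sensitivity analyses and stated limitations do not mention referral mix.

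Added patients could be healthier (otherwise home without services) or sicker (otherwise in a facility). The first would imitate benefit and the second would hide it.

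**Working it through.** **The plan's own figures.** Study sample gives a 23% control rate and a 7-point reduction, to 16%. 7/23 = 30.4%, as stated. The article gives no alpha, sidedness or power for its 400 per interval. One-sided 0.05 with 80% power gives 396, close to 400; two-sided 0.05 with 80% power gives 502. The sample size is not in dispute here. The figures carried forward are 23%, 7 points and the expected 869 per period.

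**Room for a shift.** Background says up to one-third of survivors go to home health care, so about two-thirds or more lie outside the cohort. A 20% rise in referrals means moving from 33.3% to 40% (1.2 × 33.3%).

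**Crude effect of mix, no treatment effect.** Let a be the added referrals as a fraction of the existing ones and r their readmission risk. Both are assumptions; the article gives neither.

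New rate = (0.23 + a × r) / (1 + a)

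| a | r | Calculation | New rate | Shift (points) | Relative to 7 points |
|---|---|---|---|---|---|
| 10% | 12% | 0.242/1.1 | 22.0% | -1.0 | 14% |
| 20% | 12% | 0.254/1.2 | 21.2% | -1.8 | 26% |
| 10% | 30% | 0.260/1.1 | 23.6% | +0.6 | 9%, opposite sign |
| 20% | 30% | 0.290/1.2 | 24.2% | +1.2 | 17%, opposite sign |

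**Chance of a false significant reduction.** Assume 869 per period, two-sided 0.05, and neither clustering nor adjustment. With d the shift, SE0 the pooled and SE1 the unpooled standard error, the chance is Φ[(d − 1.96 × SE0)/SE1], against a nominal 2.5%.

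- a = 20%, r = 10%: rate 20.8%, d = 0.0217, both SEs about 0.0198; Φ(−0.87) = 19%.
- a = 20%, r = 15%: rate 21.7%, d = 0.0133, both SEs about 0.0200; Φ(−1.29) = 10%.
- Referral rising only to 35%, r = 10%: shift −0.6 point, chance about 5%.

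These are illustrations for the crude two-period comparison, not for the planned mixed model.

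**Could mix alone give 7 points?** The share of the intervention cohort that would have to be newly referred is 0.07/(0.23 − r). This is 0.07/0.13 = 54% at r = 10% and 0.07/0.11 = 64% at r = 12%.

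**Can the share referred be computed?** Its denominator is all live sepsis discharges at a hospital. A request keyed to a home health claim omits survivors who never used home health care. It may catch some stays of people who used it at another time, which gives only part of the denominator. The Analysis wording implies the full hospital set. The two statements are not reconciled.

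**The case against.** The strongest reply is that nothing commits the team to changing referral. Table 2 is an interview guide, strategies are chosen for the named components, and physicians must certify eligibility for home health care. This stands. A reader might infer from Objective 2 that the study intends to raise referral; the article does not say so. What remains is a possible side effect of discussing referral barriers with the staff involved and of flagging sepsis before discharge.

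A second reply is that a shift would not be invisible. Dyad home health volume and case mix at home health admission can be tracked, and the Analysis section may mean a full hospital file. This also stands in part, so it would be wrong to read the plan as unable to show any shift. But volume alone cannot separate more referral from more sepsis admissions, and it would miss one kind of patient replacing another.

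Third, the plan adjusts for diagnoses, length of stay, function and living arrangements, so only the unmeasured remainder matters. That is right, and the figures above are crude for that reason.

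Fourth, the Background remark that "many hospitalized patients prefer to recover at home due to skilled nursing facility capacity and safety concerns" might be taken as evidence of a shift at the dyads. It describes a general trend, which concurrent national controls can address.

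Last, the study question concerns survivors receiving home health care, so some conditioning is inherent, and sensitivity analyses are commonly left to an analysis plan. The data request is different: the article states it, and a later plan cannot analyse discharges that were never obtained.

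**Conclusion.** The concern holds as a possible selection path that the stated safeguards do not fully close and that the claims request as worded would not allow to be measured. It is not a demonstrated bias. Direction and size are unknown. With 10% to 20% more referrals, 12% to 30% risk in the added patients, no adjustment and no treatment effect, the crude dyad rate moves by about -1.8 to +1.2 points. That is at most about a quarter of the 7-point target, and covariate adjustment would remove the measured part. A reader might infer that mix could account for the whole target effect. It could do so only if more than half of the intervention cohort were newly referred at 10% risk, and nothing in the article suggests that. The point deserves action before the extract is finalised.

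**What to change.** 1. Reword the claims request in Data sources and collection, Aim 1, to include hospital-stay (MedPAR) records for all live sepsis discharges at the partner hospitals and a comparison set of hospitals, whether or not a home health claim follows. Reconcile this with the Analysis section's reference to all sepsis survivors in national hospital data.
2. Report by period, for dyads and controls, the share of live sepsis discharges referred to home health care, the home health volume and the case mix at home health admission.
3. Add one supporting sensitivity analysis of 30-day readmission among sepsis survivors discharged to the community, with or without home health care.
4. State in advance that the primary conclusion will be qualified if the share referred shifts at the dyads relative to controls.

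The cost is a somewhat larger extract from a source already listed in Table 1, plus one analysis. The article mentions budget limits for a cost analysis; using a comparison set of hospitals, not every hospital, keeps the addition contained. The wider denominator dilutes the effect, so this analysis supports the primary analysis and does not replace it.

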**Objective 3. Map the process for how and when home health is notified about the referral**
How are home health personnel notified that there is a referral to home health?
1. Who gets the notification?
2. When are they notified?
3. How are they notified?
a. Do they know the expected discharge date?
4. What IT tools are used to make the referral?
5. What are the barriers to making the referral to home health care?
6. How are the patient and family involved?
a. Who involves them?
7. We are interested in learning about areas for improvement in the process. What are some areas for improvement for the process of notifying home health of the referral?
a. What resources are needed to make improvements?
8. To make improvements in this process who should we work with?
**Objective 4. Determine what patient information is transferred during the transition to home health care**
What data elements are transferred to home health care about the referral?
1. How is the information transferred (paper, electronic, verbal)?
a. If electronic: What IT tools are used for information transfer?
b. If paper: Is this faxed or a hard copy hand off?
2. Thinking about information transfer, what challenges do you experience with transferring information from hospital to home health?
3. What makes the transfer of information easy?
4. Who sends the information and who is it intended to be received by?
5. What information is placed in the HHC record, and who uses it and for what?
6. How do nurses decide what to document as diagnoses on the OASIS?
7. Name some areas for improvement in the transfer of information and the documentation of sepsis
8. To make improvements in this process, who should we work with?
